### Outcome measures

The launch of the trial was phased across participating PCTs. Following baseline assessments, practices were randomized and the clinic launched. Eighteen months later follow-up assessments were begun, ensuring that all patients in the intervention arm had 18 months exposure to the ICCD.

#### Primary clinical outcome measure

The primary outcome measure is the proportion of participants reaching all three of the following targets - HbA_1c_ (≤7.0%), blood pressure (<140/80), and total cholesterol (<4 mmol/l), as stated in National Institute of Health and Clinical Excellence (NICE) guidelines for patients with T2DM [33].

If the primary outcome measure is achieved this would represent a significant health gain. The trial aims to detect a 10% difference in the level of control in the intervention arm practices (whether or not patients attend ICCD) compared with practices in the usual care group. Audit data suggest that, in participating practices, about 15% of patients will have this level of control at baseline. We expect an increase of no more than 5% in the control arm.

#### Secondary outcome measures

Secondary outcomes are the proportion of participants reaching targets for individual risk factors (blood pressure, HbA_1c_ or cholesterol) and 10-year risks for CHD and stroke assessed by the UKPDS risk engine [34]. In order to collect sufficient data items to use the UKPDS risk engine, the Practice Record Extraction list was amended to include:

· duration of diabetes (years)

· age at diagnosis (years)

· smoking status at time of diabetes diagnosis

Other biomedical markers include BMI and waist circumference, as well as use of medication, reported smoking, costs, quality of life, emotional adjustment, patient satisfaction and views on continuity.

#### Additional outcome measures

The study also proposes obtaining routinely collected data from all patients with T2DM in participating practices. The following data will be extracted by practice staff and all identifiers will be removed before the data is given to research staff:

1. date of diagnosis of T2DM

2. latest reading with date entered for the following (excluding data entered after the date ICCDs are launched): blood pressure, total cholesterol, HbA_1c,_ and smoking status.

3. socio-demographic data including age (years), sex, and ethnicity index of multiple deprivation score (IMD, derived from patient’s postcode, using IMD 2007).

4. practice code.

Permission to obtain the data will be sought from each participating practice. The data will be extracted by members of staff from the practice using the **M**orbidity **I**nformation **Qu**ery and **E**xport **S**yn**t**ax (MIQUEST) or similar audit tool and will be transferred into an excel file, which will not contain any personally identifiable data. Instructions on how to complete the audit will be supplied by the study team. These data will be collected from the practice by the trial coordinator and will be stored and saved according to Data Protection Act regulations.

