Practices recruited to the study are randomized to either usual care or intervention arm, with the latter having access to the new ICCD clinics. In participating practices, patients with T2DM are invited to take part in the trial. Recruited patients in both arms are given a baseline assessment by a study nurse. This includes measurement of HbA_1c_, body mass index (BMI), waist circumference, blood pressure, urine and lipids. Participating patients are asked to attend a follow-up assessment 18 months after their baseline assessments, when the same measurements are repeated. Questionnaires about quality of life, satisfaction with current services, continuity of care and health service use and personal costs are completed at baseline and follow-up. An integral economic evaluation measures costs in both groups, with a comparative assessment of marginal costs and outcomes. To deal with possible selection bias, risk factor control of all patients with T2DM in intervention and control practices will be compared using anonymised GP data. Additionally, a qualitative study is exploring the views of patients, health professionals and other stakeholders using semi-structured interviews.

The overall aim is to conduct a randomized controlled trial to evaluate the effectiveness and cost-effectiveness of community-based intermediate care clinics in the management of T2DM. Specific objectives are to:

1. Compare the following in patients with T2DM registered with practices that have access to ICCD with those that have access only to usual care:

·control of cardiovascular risk factors including glycemic, blood pressure and lipid control, and cardiovascular risk assessed by UKPDS risk engine;

·quality of life;

·satisfaction with services and continuity of care;

·referral patterns and non attendance rates;

·annual cost per patient with diabetes.

2. Estimate the difference in the cost of the resources used by patients in each arm of the trial, and the cost-effectiveness of the ICCD intervention.

3. Explore the views and experiences of patients, health professionals and other stakeholders.

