### Analysis

#### Statistical analysis

Intention-to-treat (ITT) comparisons of the two groups will be conducted, with the primary dependent variable being the proportion of patients achieving all three clinical targets at 18 months. The main analysis will be based on all patients recruited to the study. As some drop-outs and losses are inevitable, sensitivity style analyses are planned. Missing data imputation will use ‘last observation carried forward’ (LOCF). Secondary analyses will exclude all observations with missing values. Analyses will use a mixed effects logistic regression model, and will adjust for baseline characteristics at both practice and individual level. The former may include practice size and deprivation index, and the latter age, gender, BMI, ethnicity, employment status, educational level and length of time since diagnosis. Characteristics will be included using a forward selection model-building strategy, with only variables significant at the 10% level selected. Odds ratios (OR) will be estimated with 95% confidence intervals, adjusting for potential confounding variables and allowing for the effect of the cluster randomization [43].

Further analysis will examine secondary outcomes (achievement of individual targets for blood pressure, HbA1c and lipids), again adjusting for confounders and allowing for the cluster randomization. In addition, UKPDS 10-year risk scores for CHD and stroke will be analyzed using a linear mixed model.

Tertiary analysis of questionnaire responses will consider longitudinal continuity, flexible continuity, relational continuity and term and boundary continuity following the NCCSDO methodology on ‘continuity of care in type 2 diabetes’ [44]. We will also compare the levels of ICCD use by the intervention practices, and the drop-out rates for all practices.

Finally, all analyses will be re-run with added data from MIQUEST covering all diabetes patients in a practice whether recruited to the trial or not [45]. This will lessen the number of variables available, but otherwise all analyses for primary and secondary endpoints will be repeated.

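### The routine-data extract stops at clinic launch, so as specified it cannot support the all-patient repeat of the 18-month analyses

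*Protocol article*

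**What the plan says.** Four parts of the protocol article bear on this.

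- **Additional outcome measures** lists what practice staff will extract for all patients with type 2 diabetes. The clinical items are "latest reading with date entered for the following (excluding data entered after the date ICCDs are launched", namely blood pressure, total cholesterol, HbA1c and smoking status. Identifiers are removed before the research team receives the file. No other extract is described.
- **Outcome measures** gives the order of events: "Following baseline assessments, practices were randomized and the clinic launched". It continues: "Eighteen months later follow-up assessments were begun, ensuring that all patients in the intervention arm had 18 months exposure to the ICCD".
- **Background** gives the purpose of the all-patient data: "To deal with possible selection bias, risk factor control of all patients with T2DM in intervention and control practices will be compared".
- **Statistical analysis** sets the "primary dependent variable being the proportion of patients achieving all three clinical targets at 18 months". It closes by saying that "all analyses will be re-run with added data from MIQUEST covering all diabetes patients in a practice whether recruited to the trial or not". It notes that fewer variables will be available, but that "otherwise all analyses for primary and secondary endpoints will be repeated".

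**The concern.** The extract is defined by a rule that removes every reading entered once the clinics are open. The analysis that uses it repeats endpoints measured 18 months after they opened. The article does consider the limits of these data, but it names only the smaller set of variables and not the missing follow-up reading.

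The all-patient analysis is the one the article puts forward by name against selection bias, and the only one that looks beyond patients who agreed to take part. Run on pre-launch readings, it would lean towards no effect however well the clinics worked. A colleague reading the result could take it as evidence that the effect among participants does not carry over to the practice population.

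**Working it through.** **Timing.** The sequence is baseline assessment, randomization, launch, then follow-up starting 18 months later. A reading entered no later than launch precedes any exposure to the clinics. The extract as specified therefore contains no post-intervention value for any patient, recruited or not.

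**Inputs**
- Combined target met by about 15% at baseline, with a rise of no more than 5 points in the control arm (Primary clinical outcome measure).
- 20% in the control arm and 30% in the intervention arm at follow-up, ICC 0.05 (Sample size).
- 49 practices and 1,997 patients recruited (Discussion), or 1,997/49 ≈ 41 per practice.
- An average practice has 150 patients with diabetes and was expected to recruit 40 to 100 of them (Patient recruitment).

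**The plan's own figure.** For 20% against 30%, two-sided α 0.05 (sidedness assumed) and power 0.80, the continuity-corrected sample size is 313 per arm. The design effect at 72 per practice is 1 + 71 × 0.05 = 4.55. This gives 313 × 4.55 ≈ 1,424 per arm, or 2,848 in total, as stated. The planning rates and ICC can therefore be used for the illustration below.

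**Reading 1: the extract used alone.** Both arms are observed before launch, at about 15% each. The expected difference is 15% − 15% = 0, whatever the true effect.

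**Reading 2: participants' 18-month outcomes kept, pre-launch readings for everyone else, each patient counted once.**
- All patients: 49 × 150 = 7,350.
- Share with an 18-month outcome: 1,997/7,350 = 0.272. This treats every recruited patient as followed up; losses would lower it.
- Control arm: 0.272 × 20% + 0.728 × 15% = 16.4%.
- Intervention arm: 0.272 × 30% + 0.728 × 15% = 19.1%.
- Difference: 10 × 0.272 = 2.7 points.

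**Sensitivity to practice size.** The 150 is a planning average for all diabetes, while the extract covers type 2 only. With an assumed 100 patients per practice the difference is 10 × 1,997/4,900 = 4.1 points. With an assumed 200 it is 10 × 1,997/9,800 = 2.0 points. At the upper end of planned recruitment, 100 of 150, it would be 10 × 100/150 = 6.7 points, but recruitment came out near 41 per practice.

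**Power, as a rough guide.** Assume 25 practices per arm, 150 patients each and ICC 0.05. The design effect is 1 + 149 × 0.05 = 8.45, and the effective size is 25 × 150/8.45 ≈ 444 per arm.

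| Data used | Control vs intervention | Power |
|---|---|---|
| Pre-launch readings only | 15% vs 15% | none; rejection at the α level |
| Pooled, 40 of 150 recruited | 16.3% vs 19.0% | about 18% |
| Pooled, 100 of 150 recruited | 18.3% vs 25.0% | about 67% |
| 18-month readings for everyone | 20% vs 30% | about 93% |

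**The case against.** **A second extract may exist.** This is a journal article condensing a fuller protocol. Trial status reports searches still running alongside follow-up, which fits a later extract, although a late search with a back-dated cut-off fits equally well. The launch rule may have been meant for a baseline extract only. That possibility stands, and it is why the outcome is not certain. It does not remove the conflict: the only extract the article defines is listed among the outcome measures, and its exclusion is explicit, so this is not merely detail left to another document.

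**The Background sentence gives no time point.** This is fair. A pre-launch comparison of all patients can show whether practices were alike across arms and how participants compare with the rest. The firm conflict is with the Statistical analysis section; the Background conflicts only if it means control after the intervention.

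**Other protections exist.** A reader might infer that this was the only safeguard against selection bias. It is the only one the article names for that purpose, but baseline assessment preceded randomization, which guards against differential recruitment, and the models adjust for practice and patient characteristics.

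**Double counting.** A reader might infer that participants enter twice, once from trial records and once from the extract, and cannot be matched. The article does not say that the files are stacked. It says that participants' GP records carry an electronic flag, and staff extract the data before removing identifiers, so participants could be marked or left out at source. What stands is that no such step is stated.

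**The analysis is supplementary.** This is true, and it limits the reach of the problem.

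**Conclusion.** The extract as specified cannot provide the 18-month outcome that the all-patient repeat of the primary and secondary analyses needs. It also cannot support a post-intervention comparison of risk factor control.

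The effect on the result depends on how the data are used: null in expectation if the extract stands alone, diluted from 10 to about 2.7 points if participants' own outcomes are kept. The second figure rests on 150 patients in each of 49 practices, each counted once; with fewer type 2 patients per practice the dilution is smaller.

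A reader might go further and say that the analysis will show a spurious null. The documents do not support that. Pooling gives dilution, chance imbalance before launch could produce a non-zero difference, and the entry dates in the file would let an analyst see that the readings are early.

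**What to change.** Reconcile Background, Additional outcome measures and Statistical analysis as follows.

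1. Extract two dated readings per patient for each risk factor: the latest before launch, as baseline, and one around 18 months after launch within a window stated in advance. Apply the launch cut-off to the first reading only. Because launch was phased, use the relevant area's launch date in both arms.
2. State how each patient is counted once, for example by analysing the MIQUEST file alone or by having practices flag participants before identifiers are removed.
3. Limit the repeat to endpoints that the extracted variables can support, and list them.
4. If a follow-up extract already exists, describe it and its dates; the query then needs no change.

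The text changes are short. The real cost is a repeat query by staff in practices already searched, at most 49. Searches were still under way at submission, so the remaining practices could use the amended query directly.

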#### Patient assessments

Patient assessments are being conducted by a trained researcher on practice premises, using standard operating procedures. Baseline assessments are necessary as GP data are non-standardized and will be up to a year old. It is not feasible for researchers to be blinded to allocation, but outcome measures are all objective; an automated sphygmomanometer is used and results of laboratory blood analyses are extracted from GP or local hospital systems. As assessments take place throughout the day, obtaining fasting blood samples is not feasible.

Patient biomedical markers consist of blood pressure, blood lipids, HbA_1c_, BMI, waist circumference, proteinuria, miroalbumiuria and self-reported smoking. In addition to the European Quality of Life-5 Dimensions (EQ-5D) standardized measure of health status developed by the EuroQol Group [35], health status is also being assessed using the short version of World Health Organization’s Quality of Life. We are also assessing satisfaction with services using the Diabetes Treatment Satisfaction Questionnaire (DTSQ) [36] emotional functioning using the Problem Areas in Diabetes (PAID) scale [37]) and continuity of care using a Continuity of Care Questionnaire [38,39]. All these questionnaires are used at both assessments. Additionally, the baseline assessment includes demographic data and prescribed medication. The GP records of patients are also flagged electronically to encourage reporting of death or change of GP.

GPs will be informed of results contributing to national Quality and Outcomes Framework (QOF) indicators which reward GP practices for the provision of ‘quality care’. These include blood pressure, weight/BMI, HbA_1c_, lipids, microalbuminuria and smoking status. This is done because it is possible that patients attending for a research assessment may be less likely to attend for routine clinical assessments.

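### The all-patient MIQUEST extract stops at clinic launch, so it cannot repeat the 18-month endpoint analyses assigned to it

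*Protocol article*

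**What the plan says.** All references are to the Protocol article.

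- **Additional outcome measures** describes "obtaining routinely collected data from all patients with T2DM in participating practices". Item 2 sets which blood pressure, cholesterol, HbA1c and smoking entries are taken: the "latest reading with date entered for the following (excluding data entered after the date ICCDs are launched". The same section states that "all identifiers will be removed before the data is given to research staff".
- **Outcome measures** (opening paragraph) gives the sequence: baseline assessment, randomization, clinic launch. Then: "Eighteen months later follow-up assessments were begun, ensuring that all patients in the intervention arm had 18 months exposure to the ICCD".
- **Statistical analysis** makes the 18-month proportion meeting all three targets the primary dependent variable. It ends by planning that "all analyses will be re-run with added data from MIQUEST covering all diabetes patients in a practice whether recruited to the trial or not". It accepts that fewer variables will be available, but "otherwise all analyses for primary and secondary endpoints will be repeated".
- **Background** (study overview) names selection bias as the reason for this comparison: "risk factor control of all patients with T2DM in intervention and control practices will be compared using anonymised GP data".

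**The concern.** A reading entered before a clinic opened cannot reflect that clinic. The extraction rule therefore leaves only pre-intervention values in both arms, while the analysis section treats the same data as able to carry the 18-month endpoints. The two statements cannot both be followed.

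What is at stake is how the trial result is interpreted. The all-patient comparison is the analysis that the article assigns to selection bias. Run on pre-launch readings, it would tend to show no difference between arms even if the clinics worked, and a reader could then take a real effect in recruited patients for an artefact of who was recruited. If the trial itself found nothing, the same analysis would seem to corroborate that finding without containing any information on it.

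**Working it through.** **1. Time order.** Admissible extract readings are those entered up to launch. Trial outcomes are measured from 18 months after launch. The two periods do not overlap, so the extract contributes no outcome value for anyone.

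**2. The plan's own figure for the endpoint to be repeated.** Inputs (Sample size): 20% v 30%, ICC 0.05, 72 patients per practice, alpha 0.05 (taken as two-sided), power 0.80.
- Two-proportion formula with continuity correction: 313 per arm.
- Design effect: 1 + (72 − 1) × 0.05 = 4.55.
- Total: 2 × 313 × 4.55 = 2,848, as stated.

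This figure does not depend on the extract. It confirms that the effect size and ICC used below are the plan's own.

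**3. Extract analysed alone.** Practices were randomized before launch, so the expected pre-launch proportion is the same in both arms. Primary clinical outcome measure puts it at about 15%. Expected difference = 15% − 15% = 0 points for any true effect. This follows by logic. A simulation adds the chance rejection rate and a comparison with usable data. It used 49 practices (25 v 24), 150 patients each, ICC 0.05, a t-test on practice proportions and 4,000 runs.

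| True effect | Pre-launch readings: mean difference, rejection rate | 18-month readings: mean difference, rejection rate |
|---|---|---|
| 0 points | 0.0, 4.8% | 0.1, 5.2% |
| 10 points | 0.0, 4.8% | 10.0, 91.8% |
| 30 points | 0.0, 4.4% | 30.0, 100% |

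**4. Extract rows added to trial outcomes.** Let P be participants with 18-month outcomes and M the MIQUEST rows. Assume similar shares in each arm and no adjustment. The arm difference in proportions is then diluted to d × P / (P + M).
- P = 1,997 recruited (Discussion).
- M = 49 × 150 = 7,350, where 150 is the average practice's number of patients with diabetes (Patient recruitment).
- d = 10 points (Primary clinical outcome measure).
- Identifiers are removed and no de-duplication is described, so participants appear in both P and M.

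| Patients per practice | M | P / (P + M) | 10 points becomes |
|---|---|---|---|
| 100 | 4,900 | 1,997 / 6,897 = 29.0% | 2.9 |
| 150 | 7,350 | 1,997 / 9,347 = 21.4% | 2.1 |
| 200 | 9,800 | 1,997 / 11,797 = 16.9% | 1.7 |

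**5. Sensitivity.**
- If participants' duplicate rows could be removed, the share is 1,997 / 7,350 = 27.2%, or about 2.7 points.
- Sample size implies 80% retention (2,044 / 2,555). Then P is about 1,598, the share is 1,598 / (1,598 + 7,350) = 17.9%, and the effect is about 1.8 points.

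**The case against.** Several points can fairly be made for the plan.

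- **A later extract may have been intended.** The rule sits under a heading about outcome measures, Trial status has MIQUEST searches running alongside follow-up assessments, and the detailed audit instructions are not shown. All this is compatible with a follow-up extract that a condensed article left out. It does not remove the problem: the article states an exclusion, and nothing in it lifts that exclusion. It does mean that the text supports a contradiction to be reconciled, not a conclusion that outcome readings were never collected.
- **The Background statement gives no time point.** Pre-launch data on all patients can show whether practices in the two arms were comparable and whether recruits resemble all patients. That is a legitimate, narrower use. The direct clash is between the extraction rule and the Statistical analysis section.
- **Other protections exist.** A reader might infer that this was the trial's only guard against selection. The documents do not support that. Baseline assessment preceded randomization, consent was taken at the assessment appointment, and the analysis is by intention to treat with baseline adjustment. These limit differential recruitment between arms.
- **The result need not be null.** A reader might infer that the re-run must show no effect. That is true only in expectation and only for the extract alone. Chance imbalance still gives significance about 5% of the time, and if the rows are pooled with trial outcomes the effect is diluted, not abolished.
- **Analysts would notice.** Each reading comes with its date of entry, so the error might be seen before a model was fitted. This makes a misleading report less likely, but it does not make the planned analysis possible.

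**Conclusion.** The point stands as a contradiction in the stated plan. Followed as written, the MIQUEST extract cannot supply the 18-month primary or secondary endpoints, and so cannot check the treatment effect in all patients.

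That the extract alone has zero expected difference rests only on the order of events. The pooled figure of about 2.1 points in place of 10 is illustrative. It depends on an assumed number of type 2 patients per practice (the document's 150 covers all diabetes), on rows simply being added, and on the unadjusted proportion scale. The planned model estimates odds ratios.

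It would be wrong to infer that the trial's main result is compromised. The primary and secondary analyses in recruited patients use the trial's own assessments and do not depend on this extract.

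**What to change.** Reconcile Additional outcome measures with Statistical analysis.

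1. Change item 2 to extract two dated readings per patient for each risk factor: the latest before launch in that Primary Care Trust, and the latest within a fixed window around 18 months after launch. Set the window in advance and use it in both arms. Patient assessments notes that "GP data are non-standardized and will be up to a year old", so an open-ended latest reading would not serve as the outcome.
2. Use the windowed reading as the outcome and the pre-launch reading as the baseline covariate. Both come from one anonymised query, so no linkage to trial records is needed.
3. Report by arm how many patients have no reading in the window.
4. Analyse the extract as its own dataset, without pooling pre-launch rows with trial outcomes.

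If post-launch readings cannot be obtained, relabel the analysis as a baseline comparison of practices and of recruited with all patients. Then remove the statement that endpoints are repeated, and narrow the Background statement on selection bias to match.

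The cost is a revised query run by practice staff at up to 49 practices, with each practice's permission, and some patients without a reading in the window. Trial status describes the searches as still ongoing at submission, although the Discussion says follow-up finished in October 2011, so some practices may need to run the query a second time.
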